### 2. Association of bacterial vaginosis with adverse reproductive outcomes

BV has been implicated in several serious obstetric and gynecologic sequelae such as preterm birth and low birth weight, premature rupture of membranes, amniotic fluid infection, chorioamnionitis, postpartum endometritis, pelvic inflammatory disease and early pregnancy loss (16-22). More recently BV was reported to be associated with both prevalent and incident HIV infections (2,23-25), and possibly with increased rate of mother to child HIV transmission (26).

Epidemiologic studies of early pregnancy loss are difficult as most loss occur unnoticed; clinically recognized losses represent only a fraction of the total losses. A study which determined daily human chorionic gonadotropin (hCG) levels on couples trying to conceive provided an estimate of 31% pregnancy loss. Of these, 22% were not clinically recognized and 9% were clinically recognizable (27). The

association of BV with conception and miscarriage in the first trimester of pregnancy was evaluated in a cohort study in Britain (28). Among 867 women attending an assisted conception unit, the miscarriage rate was 18.5% among women with normal flora, 23.3% among women with intermediate flora and 36.1% among women with BV. BV was associated with a two-fold risk of miscarriage during the first trimester; this was equivalent to one extra miscarriage for every 6 pregnant women with BV. Most of the miscarriages were subclinical. The most likely cause of miscarriage was postulated to be preexisting endometritis complicating implantation or early embryonic development. This study, unlike others which could only show that BV during pregnancy increases risk of late abortions (29,30), was able to determine the effect of BV on early losses because date of conception was known and vaginal samples could be obtained at the time of conception. BV did not affect overall conception rate in the study among British women (28).

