All women will be tested for disturbance of vaginal flora and syphilis at the first visit (3 months postnatally) and at each subsequent visit. To determine if this treatment reduces *T. vaginalis* infection, vaginal wet mounts obtained from all women (HIV negative and positive) will be examined at each visit. Urine samples will be tested at 6, 9 and 12 months postnatal visits to confirm conception and estimate rates of early pregnancy loss. Information on the last menstrual period (LMP) and history of bleeding (or spotting) will also be collected at each visit. Abortions and stillbirths will be observed and documented throughout the follow-up period. For the secondary objective (to determine clinical and behavioral factors which facilitate or impede the long-term use of metronidazole vaginal gel in a community where use of traditional vaginal agents is common) qualitative and quantitative clinical and behavioral data will be longitudinally collected postnatally to compare side-effects, compliance and acceptability between women who use the active product or the placebo. The information collected at each visit will pertain to events occurring during the past three months; i.e., most recent events. HIV negative women will be tested to confirm HIV seroconversion. HIV serology will be performed on the same blood sample which is used for syphilis testing.

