**D. 2. e. Syphilis testing.** Syphilis testing is mandatory during pregnancy in Malawi. After this initial syphilis testing, women will be followed longitudinally and screened for syphilis every six months

until study closure. Syphilis treatment will be provided at no cost for the woman and her partner if the test results are positive at any visit. Screening for syphilis will be performed using rapid plasma reagin (RPR) test and confirmed using *treponema pallidum* hemagglutination assay (TPHA) test.

**D. 2. f. Disturbance of vaginal flora testing.** The diagnosis of disturbance of vaginal flora and BV will be based on the presence of clinical criteria and will be confirmed by microscopic examination of vaginal smears (53) at each visit. The clinical definition is based on the following criteria: a) a vaginal pH >4.5 (measured by pH paper on a vaginal swab obtained from lateral and posterior fornices); b) an increased homogeneous vaginal discharge; c) presence of clue cells in  $\geq 20\%$  of vaginal epithelial cells (detected by mixing vaginal fluid with a drop of normal saline on a slide and examining under high power magnification); and d) a positive amine or Whiff test (performed by mixing a few drops of 10% potassium hydroxide with vaginal fluid). As we described in our previous studies (24,34), a woman with none of the clinical criteria will be described as having normal flora, only one criterion will be described as having mild disturbance, two criteria as having moderate disturbance, and three or more criteria as having severe disturbance or BV. This definition of BV is consistent with the conventional method based on Amsel's (54) criteria and could be equivalent to a score of 7-10 based on the Nugent vaginal smear gram stain scoring method (53).

**D. 2. g. Pregnancy testing.** We will use a highly sensitive commercial kit to detect hCG levels in a urine sample to detect pregnancy. Ultrasound to confirm pregnancy is not routinely available in Malawi and will not be used in this study; we will rely on the date of last menstrual period and pregnancy testing.

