**Specific aim 2.** Previous reports suggest that 20%-30% of women without treatment will lose their first post-index pregnancy (27). Table 12 presents powers to detect 33% and 50% reductions in the rates of early gestational loss of this first post index pregnancy based on 300 evaluable subjects in each group (we have assumed that 80% of these women will become pregnant again). There is virtual certainty to detect 50% reductions if pregnancy loss of 30% occurs, and >90% reduction if the rate of pregnancy loss is 20%. For a 33% reduction, there is about 80% power if the rate of loss is high (30%) and limited power if the rate of pregnancy loss is low (20%).

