### 3.2.1 Visit numbering

The METRO study will use a sequential visit numbering starting from V1 as shown below.

**Please note:** The first METRO study visit starts postnatally at 3 months; this will represent V 1. Each quarterly visit is followed by a test of cure visit one month after using the product; these one month follow-up visits are coded as 1.9, 2.9, 3.9, 4.9 (NO V 5.9 because no product is used at V5). The purpose of test of cure visits is to collect vaginal samples to determine if there has been changes in vaginal flora following use of the study product. We will also complete Acceptability and Product Monitoring forms at these visits.

The METRO study visit numbers are as follows:

**V 1:** Visit at 3 months postnatal; followed by a test of cure visit after one month (i.e., at 4 months postnatal) - ***this visit is coded V1.9.***

**V 2:** Visit at 6 months postnatal; followed by a test of cure visit after one month (i.e., at 7 months postnatal) - ***this visit is coded V2.9***

**V 3:** Visit at 9 months postnatal; followed by a test of cure visit after one month (i.e., at 10 months postnatal) - ***this visit is coded V3.9.***

**V 4:** Visit at 12 months postnatal; followed by a test of cure visit after one month (i.e., at 13 months postnatal) - ***this visit is coded V4.9.***

**V 5:** Visit at 15 months postnatal. This is the last follow-up visit (remember that the test of cure visit should occur one month after V4 when the last tube is issued).

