Primary endpoint: effect of treatment on rates of conception and early pregnancy loss. Previous reports suggest that 20%-30% of women without treatment will lose their first post-index pregnancy. Table 12.2. presents powers to detect 33% and 50% reductions in the rates of early gestational loss of this first post index pregnancy based on 300 evaluable subjects in each group (we have assumed that 80% of these women will become pregnant again). There is virtual certainty to detect 50% reductions if pregnancy loss of 30% occurs, and >90% reduction if the rate of pregnancy loss is 20%. For a 33% reduction, there is about 80% power if the rate of loss is high (30%) and limited power if the rate of pregnancy loss is low (20%).

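### The 20%-30% early-loss rate comes from daily hCG testing and is not matched to this trial's visit-based testing, so the stated power is probably too high

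*Protocol*

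**What the plan says.** The Protocol file holds a research plan and a manual of operations. Both base the power for early loss on the same rate. The manual (12.4.1) says: "Previous reports suggest that 20%-30% of women without treatment will lose their first post-index pregnancy". The research plan (D.4, Specific aim 2) has the same sentence and attaches reference 27.

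Section B.2 of the research plan describes that reference: "A study which determined daily human chorionic gonadotropin (hCG) levels on couples trying to conceive provided an estimate of 31% pregnancy loss". It then splits the figure: "Of these, 22% were not clinically recognized and 9% were clinically recognizable (27". Since 22 + 9 = 31, these are percentage points of all pregnancies. The same paragraph warns that "clinically recognized losses represent only a fraction of the total losses".

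On detection in this trial, D.1 says: "Urine samples will be tested at 6, 9 and 12 months postnatal visits to confirm conception and estimate rates of early pregnancy loss". The manual tests more often. Its visit table (3.2) shows urine pregnancy testing at quarterly and test-of-cure visits, and 3.2.1 says: "Each quarterly visit is followed by a test of cure visit one month after using the product". D.2.g rules out ultrasound: "we will rely on the date of last menstrual period and pregnancy testing". D.1 also collects menstrual and bleeding history at each visit and documents abortions and stillbirths throughout follow-up.

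The endpoint (D.4; manual 12.2.1) is the proportion of pregnancies lost in the first 14 weeks. Table 12 assumes 300 evaluable subjects per group. It gives power of .54 and .91 (33% and 50% reductions) at 20% loss, and .78 and .99 at 30%.

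**The concern.** A loss rate depends on how closely one looks for pregnancies. In the source, 22 of the 31 points of loss (71%) were clinically silent and came to light through daily hCG. A silent loss that begins and ends between two study tests leaves no record here, either as a pregnancy or as a loss. The plan carries the daily-testing rate over to a much coarser schedule without a discount.

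If the observable rate falls below the lowest row of Table 12, the trial has less power for this primary endpoint than it states, and a null result could be read as evidence against the treatment when few losses were detectable.

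The endpoint has a related problem. Visit-based testing brings pregnancies under observation at different gestational ages. One first detected at 10 weeks has already survived most of the 14-week risk period, while one detected at 4 weeks has not. A simple proportion lost treats them alike.

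**Working it through.** **Inputs.** Per 100 conceptions in the cited study (B.2): 22 silent losses, 9 recognised losses, and 100 - 31 = 69 continuing pregnancies. From Table 12: 300 per arm and reductions of 33% and 50%. The test is Fisher's exact (D.4; 12.4.1).

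**1. Reproduce the plan's figures.** Exact Fisher power by full enumeration, 300 per arm, one-sided .025:

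| Control loss | 33% reduction: computed (stated) | 50% reduction: computed (stated) |
|---|---|---|
| 20% | .54 (.54) | .92 (.91) |
| 30% | .78 (.78) | .99 (.99) |

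The stated one-sided .05 does not reproduce the table: it gives .66/.96 at 20% and .86/1.00 at 30%. The comparison below therefore uses one-sided .025, like for like with Table 12.

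**2. Observable loss rate.** Let d be the share of silent losses caught by a study test, and suppose all recognised losses are captured by test, history or documentation. Per 100 conceptions, losses seen = 9 + 22d and pregnancies seen = 69 + 9 + 22d = 78 + 22d. So

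observable rate = (9 + 22d)/(78 + 22d).

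**3. Plausible d.** The documents give no figure for how long a silently lost pregnancy stays hCG-positive. Assume 1-2 weeks. The manual has 8 post-baseline tests in the year (V1.9 to V5), so d is about 8 x 1/52 = .15 to 8 x 2/52 = .31.

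- d = 0: 9/78 = 11.5%
- d = .15: 12.3/81.3 = 15.1%
- d = .31: 15.82/84.82 = 18.7%

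On the research plan's 3-monthly schedule the same window gives d = 7/90 = .08 to 14/90 = .16, or about 13%-15%. Missed visits widen the gaps. In the manual's own example (3.2.3), a woman tested on 1 February misses the April visit, gives no samples when she appears in May, and is next due on 1 July.

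**4. What the tabulated rates require.** Solving for d gives d = (78q - 9)/(22(1 - q)) for a rate q.

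- q = .20: (15.6 - 9)/17.6 = .375, an hCG-positive window of about 17 days on the manual's schedule (d = 2w/90 for a window of w days)
- q = .30: (23.4 - 9)/15.4 = .94, so nearly every silent loss would have to be caught

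**5. Power at the observable rates**, 300 per arm, one-sided .025:

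| Control loss | 33% reduction | 50% reduction |
|---|---|---|
| 11.5% | .30 | .67 |
| 15% | .40 | .80 |
| 18.7% | .51 | .90 |
| Table 12, 20%-30% | .54-.78 | .91-.99 |

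At the stated one-sided .05, 11.5% loss gives .42 and .78. The 300 per arm is taken as given; whether that many pregnancies occur is a separate question.

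**The case against.** A reader might infer that most losses cannot be seen and that the tabulated rates are out of reach. The documents do not support either statement.

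- Recognised losses between tests are not lost to the trial. D.1 collects bleeding history and documents abortions, and the manual (3.2.4) provides for unscheduled visits. At d = .31 about half of all the source's losses are seen (15.82/31 = 51%); at d = .15, 40% (12.3/31).
- A 20% rate is not excluded. The 9 recognised points come from couples trying to conceive. Half the women here are HIV infected and BV is assumed in 30%. B.2 reports a two-fold first-trimester miscarriage risk with BV and more pregnancy loss with HIV. As illustration only, a relative risk of 2 in 30% of women raises 9 points to 9 x 1.3 = 11.7. Using that in the numerator and keeping the same denominators, the rate becomes 15.0%, 18.4% and 21.8% at d = 0, .15 and .31.
- At d = .31 the power, .51/.90, is close to the stated .54/.91 for 20% loss.
- Limited power is partly disclosed. D.4 calls it limited for a 33% reduction at 20% loss, and D.6 lists losses of 20% or less as a limitation.
- Survival methods for censored events are already planned (D.4; 12.6), and details such as delayed entry are commonly left to the SAP.

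These points stand, and they limit the claim. They do not restore the planning rate. D.6 attributes weak power to rare events, not to the testing schedule. The miscarriage rates of 18.5%-36.1% in B.2 do not help either: they come from an assisted-conception unit with known conception dates, and B.2 says most of those losses were subclinical.

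**Conclusion.** The concern holds as a mismatch between the source of the loss rate and this trial's means of detection. On the source's own split, the observable control rate is about 11.5%-19%, with power of .30-.51 for a 33% reduction and .67-.90 for a 50% reduction. The 20% row is doubtful but possible if BV or HIV raises recognised loss or if silent pregnancies stay detectable for longer than about 17 days. The 30% row, where a 50% reduction is described as virtually certain to be found, is not credible unless recognised loss is far above the source's 9 points.

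The result rests on three assumptions: the 1-2 week hCG window, full capture of recognised losses, and transfer of the 9-point recognised rate to this population. The first and third could move the rate either way; less than full capture would lower it.

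**What to change.** 1. In D.4 (Specific aim 2) and manual 12.4.1, replace the 20%-30% rate with a range matched to visit-based detection, for example about 10%-20%. State d and any uplift for BV or HIV as assumptions.
2. Recompute Tables 12 and 12.2 over that range and remove the claim of virtually certain detection at 30% loss.
3. In D.6, name incomplete detection between visits as a reason for limited power, alongside rarity.
4. In D.4 and manual 12.2.1, define the endpoint as loss by 14 weeks among pregnancies detected by a study test or clinically documented. Restricting it to losses after a positive study test would discard recognised abortions that the trial already records.
5. Analyse it with the survival methods already planned, with delayed entry at the gestational age of first detection. The detail can go in the SAP.

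The cost is a lower stated power for a primary endpoint and slightly more analysis work. No extra tests or visits are needed.

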Among African women, however, the effect of HIV, an infection which causes adverse reproductive outcomes such as abortions, low birth weight and increased perinatal mortality, needs careful consideration when assessing the association between BV and pregnancy loss. For example, in a population-based study in the Rakai district of Uganda (31), pregnancy prevalence was significantly reduced among HIV infected compared with uninfected women (23.5 vs 30.1 per 100 woman-years; adjusted risk ratio 0.73; 95% CI 0.57-0.93) due to lower rates of conception and increased rates of pregnancy loss. In the proposed study we will have the opportunity to evaluate the effect of BV treatment on pregnancy loss among separate groups of HIV infected and uninfected African women.

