**Table 12. Estimated power for specific aim 2 assuming 300 evaluable subjects in each group during the first year.**

| Normative rate of
pregnancy loss | Reduction from intervention |            |
|---------------------------------------------|------------------------------------|------------|
|                                             | 33%                         | 50% |
| 0.20                                        | .54                                | .91        |
| 0.30                                        | .78                                | .99        |

**Data management.** Data entry and storage will be conducted on-site. The Johns Hopkins Project in Malawi has trained staff who have performed this activity for over a decade. Each record will be double entered into the computer and records compared. No direct subject identifiers (e.g., names, addresses, etc.) will be entered into data sets. The data will be stored on secure computers in Malawi and Johns Hopkins University. All original data collection forms will be kept in locked file cabinets. Data entry and management procedures are described further under Quality Control and Assurance (section D. 5). FoxPRO and SAS for windows are available for data management in Malawi. Computers used in the study are protected against computer virus attack by Norton antiviral software. All data sets are backed up onto tapes on a weekly basis both at Malawi and Johns Hopkins University (JHU). For this study we propose to manage the data locally in Malawi and perform further management and data analyses at JHU in Baltimore. The data will electronically be transferred to Baltimore.

**Data analysis.** Analyses will be done using an intention to treat approach. Separate analyses for HIV infected and uninfected women will be performed and the effect of the intervention on outcomes in these two groups will be compared. The effect of the intervention will be based on comparing incidence of BV and portion of pregnancy losses between treated and untreated (control) subjects.

Multiple hypotheses will be tested in this study, requiring a diverse array of analytical methods

 Although we use the term incidence in the text, it is more accurate to define this measure as cross-sectional prevalence because the number of BV cases during a 3 month interval are a combination of new and continuing cases (due to incomplete cure and recurrences).

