For some analyses we will pool repeated measurements from the same individual over multiple study visits. For example, occurrence of BV across all post-intervention study visits will be compared between study groups. For these analyses, generalized estimation equation models, which use an individual as cluster unit, will be fit to obtain robust covariance. For binary outcomes, a logit link will be used.

Data monitoring and reporting. This trial will be monitored by a Data and Safety Monitoring Board (DSMB). Formal interim analyses of efficacy of the intervention, based on the primary endpoints, will then be performed at approximately six month intervals during the projected study duration. Recommendations for early termination of positive or negative results will be guided by the symmetric group sequential O'Brien-Fleming Boundary (58). The O'Brien-Fleming design allows for early termination if extreme initial results are seen, while essentially allowing employment of the standard single stage one-sided 0.025-level test statistic at the final analysis if it is reached. This enables one to maintain the power of the single-stage design in the presence of interim monitoring without having to increase the maximum sample size. As has been the plan for other clinical trials conducted by our research team in Malawi, we will arrange for regular dissemination of information.

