## 11.2 Adverse experiences

### 11.2.1 Summary

Intravaginal metronidazole gel is recommended by the Centers for Disease Control (CDC) for treatment of BV and no major risks have been reported when used in non-pregnant women. Minor complaints include yeast infection, vaginal irritation and rash. We will perform a wet mount at each visit (and at interim visit, if necessary) to monitor these infections and will provide treatment when clinically indicated. Information on use of the gel during pregnancy is limited. Therefore, the gel will be stopped if a woman becomes pregnant while using the gel. The dose of metronidazole intravaginal gel is very small compared to a usual oral metronidazole dose (about 188 mg intravaginal compared with 5000 mg oral). Additionally, systemic absorption of intravaginal gel was reported to be very low. Because some interactions have been reported between oral metronidazole use and alcohol, we will advise women not to drink alcohol while using the gel.

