#### 12.3.1 Instructions for using the allocation study ID's

##### By Whom

Study coordinator (as the rest of the study investigators and workers, the study coordinator is completely blinded about the treatment assignment).

Procedure

1. Assign these Lists to the five Study Clinics as shown in section 12.3. above
2. Each woman enrolling in the study will be sequentially assigned the next available ID in each clinic.

12.4 Sample size and analysis plan12.4.1 Sample size and power:

The following design specifications will apply: number of treatment groups: 2; follow-up period: approximately one year; hypotheses will be tested using a one-sided type 1 error of  $\alpha=0.05$ . Unless stated otherwise, powers are obtained based on Fisher's exact test for comparisons of proportions in two groups.

We will recruit 1664 women of whom 832 will be HIV infected and 832 will be uninfected. In each group of women, 416 will be randomized to treatment arm and 416 to placebo arm. Based on previous experience in Malawi, losses due to dropouts and non-compliance will be less than 10% per year. Thus at least 375 women in each arm will return to each study visit during the first year.

Primary endpoint: effect of treatment on BV incidence. Power estimates for this primary endpoint are shown in Tables 12.1. In previous studies from Malawi, cross sectional prevalence of BV among untreated women was 30% and that of any vaginal disturbance was 89%.

**Table 12.1. Estimated power for specific aim 1 (comparing BV at each visit during the first study year assuming at least 375 evaluable study subjects in each group).**

| Normative rate
in untreated women | Reduction from intervention |       |
|--------------------------------------|------------------------------------|-------|
|                                      | 33%                                | 50%   |
| 0.30                                 | .87                         | ~1.00 |
| 0.89                                 | ~1.00                       | ~1.00 |

Thus there will be **0.87** and almost **1.00** power to detect 33% reductions in cross sectional visit prevalence of BV (normative rate 0.30 in untreated subjects) and any vaginal flora disturbance (normative rate .89 in untreated subjects).

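### Pregnancy-loss power rests on an unsourced 80% conception rate in one year, 5 to 7 times the only pregnancy rate the protocol cites; at the cited rates every stated power falls well short

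*Protocol*

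**What the plan says.** The power text for pregnancy loss appears twice, in D.4 (Specific aim 2) and in section 12.4.1 of the manual of operations. Each HIV stratum is sized separately: "In each group of women, 416 will be randomized to treatment arm and 416 to placebo arm". With losses below 10%, about 375 women per arm are expected at each visit. For pregnancy loss, "we have assumed that 80% of these women will become pregnant again", which gives 300. The caption of Table 12 fixes the time frame: "Estimated power for specific aim 2 assuming 300 evaluable subjects in each group during the first year". Its four powers are .54 and .91 at 20% loss, and .78 and .99 at 30% loss, for 33% and 50% reductions. The text describes a 50% reduction as virtually sure to be detected at 30% loss, gives a figure above 90% at 20% loss, and gives about 80% for a 33% reduction at 30% loss.

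On method, "powers are obtained based on Fisher's exact test for comparisons of proportions in two groups" and "hypotheses will be tested using a one-sided type 1 error of" 0.05. The monitoring paragraph of D.4 instead refers to a "standard single stage one-sided 0.025-level test statistic at the final analysis".

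The only pregnancy rate in the document is in section B.2: "23.5 vs 30.1 per 100 woman-years", from a population-based study in Uganda. On product use, section 11.2.1 says that "the gel will be stopped if a woman becomes pregnant while using the gel", and addendum 13.3 keeps these women in follow-up.

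**The concern.** Power for a loss proportion depends on how many pregnancies occur, and 300 per arm per stratum is the weakest input in the table. It has no citation, while the protocol's own background gives a rate that points to about a third of that number. The women are also recruited mainly about three months after delivery, in a setting where the protocol describes breastfeeding as universal.

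Pregnancy loss is a primary endpoint. If far fewer women conceive, the trial could not reliably detect even a halving of loss within either HIV stratum, although the tables say it could. A null result would then look more informative than it is. Section D.6 concedes weakness only when losses are rare (20% or less). It does not name the number of pregnancies as a risk.

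**Working it through.** **Inputs.** 375 evaluable women per arm per stratum; 80% conceiving; about one year of follow-up; control loss 0.20 and 0.30; relative reductions 33% and 50% (D.4, 12.4.1). Cited rates 0.235 and 0.301 per woman-year (B.2).

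**1. Reproduce the stated figures.** With p_T = p_C(1 − r), exact power is the sum of Bin(x_T; n, p_T) × Bin(x_C; n, p_C) over all outcomes where the one-sided hypergeometric tail is at most α. The count is 375 × 0.80 = 300. The cells of Table 12.2 are not in the text at hand, so Table 12 is used.

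| Loss, reduction | Stated | α = 0.025 | α = 0.05 |
|---|---|---|---|
| 30%, 33% | .78 | .775 | .858 |
| 30%, 50% | .99 | .992 | .997 |
| 20%, 33% | .54 | .543 | .662 |
| 20%, 50% | .91 | .920 | .957 |

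The table arithmetic is sound, but it matches one-sided 0.025, not the 0.05 named in the power text. The results below use 0.025 unless stated.

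**2. Rate implied by 80%.** −ln(1 − 0.80) = 1.61 per woman-year, or 161 per 100 woman-years. Ratios to the cited rates: 1.61/0.301 = 5.3 and 1.61/0.235 = 6.8.

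**3. First pregnancies at the cited rates.** The endpoint is loss of a woman's first post-index pregnancy, so at most one counts per woman: n = 375 × (1 − exp(−rate)).
- HIV infected: 375 × (1 − exp(−0.235)) = 375 × 0.209 ≈ 79.
- HIV uninfected: 375 × (1 − exp(−0.301)) = 375 × 0.260 ≈ 97.

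**4. Power at those counts, and at twice the rate.** Doubling without conversion to first pregnancies, a generous reading, gives 375 × 0.470 = 176 and 375 × 0.602 = 226.

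| Loss, reduction | Stated (n = 300) | n = 79 to 97 | n = 176 to 226 |
|---|---|---|---|
| 30%, 33% | .78 | .241 to .301 | .529 to .643 |
| 30%, 50% | .99 | .556 to .654 | .908 to .964 |
| 20%, 33% | .54 | .145 to .182 | .329 to .422 |
| 20%, 50% | .91 | .343 to .429 | .707 to .823 |

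At one-sided 0.05, n = 79 to 97 gives .35 to .42, .68 to .76, .23 to .28 and .47 to .55 in the same order. These are also below every stated value.

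**5. Consequence for the BV power.** Table 12.1 gives .87 for a 33% reduction from 30% BV at each visit; Fisher at n = 375 gives .865. Suppose the 33% is an on-product effect, conceptions occur at a constant hazard, and earlier courses have no carry-over. The net reduction at a visit is then 0.33 × exp(−rate × t), where t is the time from enrolment to the preceding course. Pregnant women are excluded at enrolment, so V2 is unaffected.

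| Visit | t (years) | Share already pregnant | Net reduction | Power |
|---|---|---|---|---|
| V2 | 0 | 0 | .330 | .865 |
| V3 | 0.25 | .057 to .072 | .311 to .306 | .819 to .805 |
| V4 | 0.50 | .111 to .140 | .293 to .284 | .767 to .737 |
| V5 | 0.75 | .162 to .202 | .277 to .263 | .713 to .667 |

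**The case against.** **The benchmark is not a planning rate.** The Ugandan figure is labelled pregnancy prevalence and is cited to show the effect of HIV. It may miss early losses, whereas this trial tests urine hCG at quarterly and one-month visits and, by addendum, enrols sexually active women outside the postnatal clinics. Section B.2 reports 22% of pregnancies lost before clinical recognition. Scaling the unconverted counts of 88 and 113 (375 × 0.235 and 375 × 0.301) for that gives 88/0.78 = 113 and 113/0.78 = 145. This stands: no single replacement for 300 can be prescribed. It does not rescue the 300, because even doubled rates leave every cell short.

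**The protocol already admits some weakness.** It calls power limited for a 33% reduction at 20% loss, and D.6 repeats a caution about rare losses. That is fair, but both caveats concern the loss rate. Neither concerns the number of pregnancies.

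**The two power tables.** Because the gel stops in pregnancy, a reader might infer that the BV and pregnancy-loss tables cannot both be true. The documents do not support that. Analysis is by intention to treat, so the 33% in Table 12.1 can be read as a net effect that already allows for stopped product. Power at V3, V4 and V5 would fall as low as about .51, .25 and .13 only if the doubtful 80% were true and the 33% were an on-product effect without carry-over. At the cited rates the erosion is moderate.

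**Pooling.** A reader might also conclude that pregnancy loss should be tested once across HIV strata. That would change the planned separate analyses. With about 79 + 97 = 176 first pregnancies per arm, it would still fall short of the stated figures.

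**Conclusion.** The point holds. The stated power for a primary endpoint depends on an unsourced conception proportion that, as a hazard, is 5 to 7 times the only rate in the protocol. At the cited rates the four powers fall from .78, .99, .54 and .91 to about .24 to .30, .56 to .65, .15 to .18 and .34 to .43.

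This size assumes that the Ugandan rates apply to this cohort, that each woman contributes one year at a constant hazard, and that the test level is one-sided 0.025. The direction is robust: it persists at one-sided 0.05 with the cited rates, and at one-sided 0.025 with twice those rates. The fault lies in the 80% input, not in the power arithmetic.

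The link to Table 12.1 is secondary. It asks for consistent assumptions and a clear definition of the 33%, and does not show a contradiction.

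**What to change.** 1. In D.4 and 12.4.1, replace the single 80% (300 pregnancies) with a range of conception rates that includes the cited ones: about 80 to 100, up to about 225, pregnancies per arm per HIV stratum. If 80% is kept as one scenario, give its source.
2. Restate Tables 12 and 12.2 over that range, and revise the sentences that claim near-certain detection, a figure above 90%, and about 80% power. State the test level that the tables actually use.
3. In D.6, add the number of pregnancies as a limitation alongside the loss rate.
4. In Table 12.1, use the same conception rates and say whether the 33% is a net effect or an on-product effect. If it is on-product, show power by visit.
5. Optionally, add a pooled, HIV-stratified estimate of pregnancy loss as supportive, leaving the planned separate analyses in place.

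These are changes to text and tables only and need no extra participants or procedures. The cost is that the stated power becomes less favourable.
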